**Introduction**

INDUCTION OF LABOUR

Induction of labor is a procedure used to stimulate uterine contractions during pregnancy before spontaneous labor. Successful labor induction leads to a vaginal birth. A health care provider might recommend labor induction for various indications, primarily when there's concern for a mother's health or a baby's health. In developed countries, up to 25% of all deliveries at term now involve induction of labor. In developing countries, the rates are generally lower, but in some settings they can be as high as those observed in developed countries,(World Health Organization, WHO(3)

Induction of labor is not risk-free and many women find it to be uncomfortable. With a view to promoting the best known clinical practices in labor and childbirth and to improving maternal outcomes worldwide, WHO has developed the present recommendations using the procedures outlined in the *WHO Handbook for guideline development(3)*

General principles related to the practice of induction of labor

Induction of labor should be performed only when there is a clear medical indication for it and the expected benefits outweigh its potential harms.

In applying the recommendations, consideration must be given to the actual condition, wishes and preferences of each woman, with emphasis being placed on cervical status, the specific method of induction of labor and associated conditions such as parity and rupture of membranes.

Induction of labor should be performed with caution since the procedure carries the risk of uterine hyper stimulation and rupture and fetal distress.

Wherever induction of labor is carried out, facilities should be available for assessing maternal and fetal well-being.

Women receiving oxytocin, misoprostol or other prostaglandins should never be left unattended.

Failed induction of labor does not necessarily indicate caesarean section.

Wherever possible, induction of labor should be carried out in facilities where caesarean section can be performed.

The indication for induction of labor therefore must be convincing, compelling, consented to and documented. These conditions are not met when the proposed indication is solely for the convenience of the physician or the woman alone.

Specific recommendations for induction of labor

1. Induction of labor is recommended for women who are known with certainty to have reached 41 weeks (>40 weeks + 7 days) of gestation.
2. Induction of labor is not recommended in women with an uncomplicated pregnancy at gestational age less than 41 weeks.
3. If gestational diabetes is the only abnormality, induction of labor before 41 weeks of gestation is not recommended.
4. Induction of labor at term is not recommended for suspected fetal macrosomia.
5. Induction of labor is recommended for women with prelabour rupture of membranes at term.
6. For induction of labor in women with an uncomplicated twin pregnancy at or near term, no recommendation was made as there was insufficient evidence to issue a recommendation. If prostaglandins are not available, intravenous oxytocin alone should be used for induction of labor. Amniotomy alone is not recommended for induction of labor.

Methods of induction of labor

Methods of labor induction include mechanical and pharmacological means. Optimal choice of these depends on the pre-induction status of the cervix. The three factors most likely to lead to success include favorable cervix, multiparity and prior vaginal delivery. The cervix is considered unfavorable if the bishop score is less than 6.The most important element of bishop score is dilation, followed by effacement, station and position, with the least useful element being cervical consistency. Xenakis et al clearly demonstrated that women who had a bishop score of 3 or less at onset of induction had significantly higher rates of failed induction and caesarean delivery then those with a bishop score above 3.

Table 1-Bishop scoring system.

| Factor | 0 | 1 | 2 | 3 |
| --- | --- | --- | --- | --- |
| Dilatation (cm) | 0 | 1-2 | 3-4 | >5 |
| Effacement (%) | 0-30 | 40-50 | 60-70 | >80 |
| Consistency | Firm | Medium | Soft |  |
| Position | Posterior | Central | Anterior |  |
| Station | -3 | -2 | -1 or 0 | +1 or lower |

WHO has proposed the following recommendations,

1-If prostaglandins are not available, intravenous oxytocin alone should be used for induction of labor. Amniotomy alone is not recommended for induction of labor.

2- Oral misoprostol (25 μg, 2-hourly) is recommended for induction of labor.

3- Low-dose vaginal misoprostol (25 μg, 6-hourly) is recommended for induction of labor.

4- Misoprostol is not recommended for induction of labor in women with previous caesarean section.

5- Low doses of vaginal prostaglandins are recommended for induction of labor.

6-Balloon catheter is recommended for induction of labor.

7-The combination of balloon catheter plus oxytocin is recommended as an alternative method of induction of labor when prostaglandins (including misoprostol) are not available or are contraindicated.

8-In the third trimester, in women with a dead or an anomalous fetus, oral or vaginal misoprostol are recommended for induction of labor.

9- Sweeping membranes are recommended for reducing formal induction of labor.

MANAGEMENT OF ADVERSE EFFECTS ASSOCIATED WITH INDUCTION OF LABOUR

Betamimetics are recommended for women with uterine hyper- stimulation during induction of labor. Uterine hyper stimulation is defined as either occurrence of uterine contractions lasting more than 60 seconds, or occurrence of more than four contractions within 10 minutes, regardless the state of the fetus.Terbutaline is the main beta mimetic used.Tocolytics like magnesium sulfate,atosiban and nitroglycerin have a small effect(3).

Setting for induction of labor

Outpatient induction of labor is not recommended for improving birth outcomes. This because induction of labor requires facilities for monitoring maternal and fetal well-being. Secondly induction should be done in a facility which has the capacity of doing a cesarean section(3).

**DEFINITION OF FAILED INDUCTION**.

Failed induction is defined as labor not starting after one cycle of treatment or after 24 hours. If induction fails, healthcare professionals should discuss this with the woman and provide support. The woman’s condition and the pregnancy in general should be fully reassessed, and fetal wellbeing should be assessed using electronic fetal monitoring. If induction fails, decisions about further management should be made in accordance with the woman’s wishes, and should take into account the clinical circumstances. The subsequent management options include: a further attempt to induce labor (the timing should depend on the clinical situation and the woman’s wishes) or caesarean section.(7). A study done by Osaheni Lucky et al. (Nigeria, 2014) found out 24.1% rate of failed induction. Locally, a study done by Esiromo (KNH, 2011) found out 26% rates of failed induction. The study also found out 77.7% success rate with misoprostol alone and 40% success with Foleys catheter alone.

**Predictors of successful induction of labor**.

Successful induction of labor is more likely if there is a good Bishop score, more than 3,multiparity and Prior vaginal delivery. Xenakis et.al clearly demonstrated that women who had a bishop score of 3 or less at onset of induction had significantly higher rates of failed induction and caesarean delivery then those with a bishop score above 3.

**CONCEPTUAL FRAMEWORK**

Women for induction of labour

Those recruited and allocated the combination arm

Those recruited and allocated misoprostol arm

Misoprostol and Foley catheter administered as per protocol

Misoprostol administered as per protocol

Increased intracellular calcium,elastase and GAGs

Increased intracellular calcium,elastase and glycosaminoglycan.local pressure effect of the balloon on the cervix

Cervical dilatation and onset of labour.

Faster cervical dilatation of the cervix and shorter duration of labour.

**SCHEMA OF TRIAL**

**Screened**

**N=**

**Enrolled**

**N=**

**Foley catheter and misoprostol**

**N=**

**Misoprostol**

**N=**

**Primary outcome: failed induction**

**N=**

**Primary outcome: failed induction**

**N=**

**Secondary outcomes**

**N=**

**Secondary outcomes**

**N=**

**Study justification**

Failed induction or prolonged duration of induction to delivery may increase costs, patient anxiety, and if not monitored well especially in the setting of heavy workload may lead to poor neonatal outcomes.

If induction of labor using combined Foley and misoprostol can reverse or reduce these outcomes then it can change guidelines on induction of labor or for those patients at risk of failed induction.

A similar study has also not been carried out at our study setting.

**Research question**

Is there a difference in the incidence of failed induction if combined Foley catheter plus misoprostol versus misoprostol alone is used for cervical ripening and induction of labor?

**Hypothesis**

There is no difference in the incidence of failed induction when combined Foley catheter plus misoprostol versus misoprostol alone is used cervical ripening and induction of labor.

**OBJECTIVES.**

**BROAD OBJECTIVE:**

To evaluate the efficacy of combined mechanical (Foley balloon) and pharmacologic (misoprostol) administration in reducing the incidence of failed induction.

**SPECIFIC OBJECTIVES**

Among pregnant women undergoing cervical ripening and induction of labor using combined misoprostol and Foley balloon versus misoprostol alone,

1. Determine and compare the incidence of failed induction.
2. Determine and compare the induction to delivery time.
3. Determine and compare immediate maternal and perinatal outcomes.

**METHODOLOGY**

**Study design**

Two arm open label (non blind) RCT

**Study population**

Pregnant women with Bishop’s score of 6 or less presenting to KNH labor wards for labor induction

**Intervention arm**

Foley plus misoprostol

**Control arm**

Misoprostol alone

**Outcomes**

Primary outcome-failed induction

**Secondary outcome**

Induction to delivery time

Mode of delivery

Maternal outcomes-PPH, chorioamnionitis,hyperstimulation(5 contractions in 5mins)

Perinatal outcomes (APGAR, NICU admission

Methodology

Block randomization of all eligible consenting subjects by computer generated random sequences and a randomization ratio of 1:1.Upon enrollment, an opaque envelope containing the participant’s enrollment number and assignment to either the Foley plus vaginal misoprostol or vaginal misoprostol alone will be opened .Each participant will be assigned a unique 4-digit-long subject number for subject identity and confidentiality. Participants and health provider will be aware of the treatment allocation at the time of assignment of treatment.

Study procedures.

Patients who fall in the Misoprostol arm will be given 25 mcg vaginally 6hourly up to a maximum of 4 doses, Bishop score >6 or when they go into active labor. Later amniotomy and augmentation may be done as per protocol

Patients who fall in the Combination arm will be inserted an 18-French Foley catheter with a 30 cc balloon will be placed just above the internal cervical os and then inflated with 30 cc of sterile saline. The length of the Foley catheter will be affixed to the subject’s inner thigh under slight tension. At the same time 25 mcg of misoprostol is inserted at the posterior fornix of the vagina 6 hourly up to a maximum of 4 doses, Bishop score >6 or active labor. If difficult, Foley catheter insertion will be attempted every 6 hours unless Bishop score more than 6 or in active labor. When Foley balloon falls off, labor may be augmented or amniotomy performed as per the existing protocol.

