**Study population**

Pregnant women admitted for induction of labor at KNH at gestational age of 28 weeks and beyond.

INCLUSION & EXCLUSION CRITERIA:

Inclusion:

Intrauterine gestation, cephalic presentation, intact membranes, IUFD and Bishop score less than 6.

Willing to give informed consent.

Exclusion:

IUGR, Previous cesarean sections, multiple gestation, contraindication to prostaglandins, fetal anomalies, other uterine surgeries, EFW>4000G,Placenta previa, NRFS, multiparity >5,HIV infected and those not sure of dates by clinical examination as well as ultrasound dating.

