**Sample size calculation**

A recent Kenyan study placed failed induction at 26%.

We postulate that offering a combined use of misoprostol and Foley catheter will reduce this proportion to 16%.

Therefore for us to detect a 16% difference in the successful induction following the use of Foley with misoprostol versus misoprostol alone, we estimated using the sample size formula,

Sample size formula

[Allan Donner; Stat. Medicine (1984)

that we would need to study a total of 180 women (90 per group) to achieve a 80% power to detect the stated difference of 16% at a two-sided alpha=0.05 level of significance.

Where we define p_c_=74% and p_a_=90% to be the proportions of women in the misoprostol and combined misoprostol and Foley groups respectively

and = (p_C_ + p_a_)/2 ( =1.960, and =0.84

**Data collection, management and analysis**.

Data collection and storage: Data will be collected by use of questionnaires by the principal investigator and 3 or 4 well trained research assistants. Information will be obtained from history, review of medical records and clinical examination. The information will be stored safely in a password-protected computer and backed up on a dedicated USB drive. Any hard copy records carried for analysis will be stored under lock and key and patients confidentiality will be observed. A qualified statistician will do analysis as per protocol with intent to treat analysis using SPSS version 21.Primary outcome will be failed induction/successful induction and secondary outcomes include time to delivery, maternal and perinatal outcomes. Proportions will be compares using Chi2 test, 95% CI, two tailed hypothesis with p significant at <0.05

Ethical considerations.

- Permission will be sought from the KNH/UON ERC.
- Informed Consent.
- Confidentiality.
- Patients who decline to give consent will be treated as per the existing protocols and no penalty at all.

Study limitations

Non-blinding may have influence patient management

No long-term follow up of mother and neonate for late outcomes

No interim analysis due to resources.

Study timelines

- Proposal presentation-January 2014
- ERC approval and registration-February 2015
- Enrollment-march-September 2015
- Analysis-September-December 2015
- Presentation-December 2015
- Publishing-December-June 2016
- Dissemination of results-June 2016

Study budget

The anticipated expenses during this study include the following-

Buying of Foleys catheters and misoprostol-

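### The hyperstimulation outcome is set at 5 contractions in 5 minutes, twice the frequency limit in the protocol's only other definition, with no reason given

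*Protocol*

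**What the plan says.** The Secondary outcome section of the Protocol names three maternal outcomes and gives a threshold for only the last of them: "Maternal outcomes-PPH, chorioamnionitis,hyperstimulation(5 contractions in 5mins". No other section on outcomes, procedures or analysis adds to that threshold.

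The Introduction, under management of adverse effects associated with induction, defines hyperstimulation as "either occurrence of uterine contractions lasting more than 60 seconds, or occurrence of more than four contractions within 10 minutes", and adds that this holds "regardless the state of the fetus".

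The outcome serves the third specific objective, "Determine and compare immediate maternal and perinatal outcomes". For the analysis, the section on data collection, management and analysis states "Proportions will be compares using Chi2 test".

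**The concern.** The same word carries two frequency limits in one document. The limit that will be recorded is the stricter one. The protocol does not say that a stricter outcome is intended, does not grade hyperstimulation into levels, and does not explain the shorter window.

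Hyperstimulation is a safety outcome. The general principles in the Introduction warn that "the procedure carries the risk of uterine hyper stimulation and rupture and fetal distress". If the threshold is applied as printed, the reported proportion in each arm leaves out women whose contraction frequency the protocol itself elsewhere calls hyperstimulation. A reader of the results who takes the definition from the Introduction would misread the rate.

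**Working it through.** **Inputs.** Outcome threshold: 5 contractions in 5 minutes (Protocol, Secondary outcome). Comparison threshold: more than four in 10 minutes, so at least 5 whole contractions in 10 minutes (Protocol, Introduction, management of adverse effects). The outcome threshold is a stated value, not a derived one, so there is no calculation of the plan's to reproduce. The sample size of 90 per group does not enter.

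**Step 1: rates.**
- Outcome: 5 / 5 = 1.0 per minute.
- Introduction: 5 / 10 = 0.5 per minute.
- Ratio: 1.0 / 0.5 = 2.0.

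**Step 2: direction.** Any woman with 5 contractions in 5 minutes also has at least 5 within a 10-minute window that contains those 5 minutes. Every case under the outcome threshold is therefore a case under the Introduction's limit, but not the reverse. Relative to that limit, the printed threshold can only miss cases.

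**Step 3: which patterns are missed.** Assume even spacing at an interval of d minutes and count contraction starts. The most that fit in a closed window of w minutes is floor(w/d) + 1.
- Introduction: floor(10/d) + 1 ≥ 5 gives d ≤ 2.5.
- Outcome: floor(5/d) + 1 ≥ 5 gives d ≤ 1.25.

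| Interval d (min) | Most in 10 min | Most in 5 min | Introduction frequency limit | Outcome as written |
| --- | --- | --- | --- | --- |
| 1.25 | 9 | 5 | met | met |
| 1.3 | 8 | 4 | met | not met |
| 2 | 6 | 3 | met | not met |
| 2.5 | 5 | 3 | met | not met |
| 2.6 | 4 | 2 | not met | not met |

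The missed band is 1.25 < d ≤ 2.5 minutes, or 5 to 8 contractions in 10 minutes.

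**Step 4: sensitivity to the counting rule.** If the count is taken as floor(w/d), without the extra contraction at the window's edge, the limits become d ≤ 2 and d ≤ 1, and the missed band becomes 1 < d ≤ 2 minutes. The factor of two stays, and one contraction every 2 minutes is still missed.

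**Step 5: if the window is a slip.** Five in 10 minutes is the same as more than four in 10 minutes. With that one number changed, the frequency limits agree exactly and the missed band disappears.

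**The case against.** The two definitions have different roles. The one in the Introduction summarizes guideline recommendations and never says that the trial will score the outcome that way. The one among the outcomes is the only operational rule, so an assessor has a single rule to follow, applied alike in both arms. A trial may choose a stricter outcome than its background text. To speak of missed cases takes the Introduction as the standard. The 5 minutes may also be a plain slip, in which case this is a one-number correction.

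Much of that stands. A stricter outcome is legitimate if it is meant and said to be stricter, and the missed cases are missed only relative to the protocol's other definition. The even-spacing band is an illustration: five contractions clustered within 5 minutes meet both limits. But the threshold sits in the list of outcomes and governs what is recorded. If it is a slip, it should be corrected before recording starts. If it is intended, nothing in the document says so.

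A reader might infer three stronger points. The documents do not support them.
- *The outcome is defective because it lacks the over-60-seconds criterion.* The Introduction's duration criterion sets no minimum number of such contractions. It would need contractions to be timed, and in this open-label trial the staff doing so would know the allocation. Whether to include it is a debatable choice, not an error.
- *Women treated for hyperstimulation will be recorded as having had none.* The Introduction does report that "Betamimetics are recommended for women with uterine hyper- stimulation during induction of labor", but the study procedures set no such trigger for treatment, so the documents do not show that this would happen.
- *The Introduction's definition suits women with fetal demise better.* Such women are named in the inclusion criteria ("Intrauterine gestation, cephalic presentation, intact membranes, IUFD and Bishop score less than 6"), but the present threshold is also a plain contraction count that needs no fetal criterion.

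**Conclusion.** The point holds for the frequency threshold. As printed, the outcome requires twice the contraction rate of the protocol's only other definition (1.0 against 0.5 per minute), and no reason is given. With even spacing, and starts counted in a closed window, contractions more than 1.25 and up to 2.5 minutes apart fall in the gap.

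The number of women in that gap cannot be given, because the documents state no rate of hyperstimulation, and none is assumed here. A reader might infer a bias between the arms or an effect on the main result. Neither follows: the same rule applies to both arms, and failed induction and the sample size do not depend on it. This is a minor but clear correction to one secondary safety outcome, and a slip for 10 minutes is a plausible cause.

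**What to change.** In the Secondary outcome section and on the questionnaire, change the hyperstimulation threshold from 5 contractions in 5 minutes to more than four (five or more) in any 10-minute window, and apply it identically in both arms. If the sponsor does want the stricter limit, say so, give the reason, and distinguish it by name from the definition in the Introduction.

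Adding contractions of more than 60 seconds is optional. It would require contractions to be timed, and the sponsor would need to decide how many must exceed that length.

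The cost is one changed number in the protocol and the matching questionnaire item. The recorded hyperstimulation rate will probably be higher in both arms. Dosing, the primary outcome and the 90 women per group do not change.

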**ABSTRACT**

The World Health Organization (WHO) defines induction of labor as the initiation of labor by artificial means prior to its spontaneous onset at a viable gestational age with the aim of achieving vaginal delivery in a pregnant woman with intact membranes. Successful labor induction leads to vaginal birth while failed induction is the inability to achieve more than 3 cm cervical dilatation after 24 hours of induction of labor. In developed countries, up to 25% of term deliveries involve induction of labor compared to about 9.6% in the developing countries (6). Failed induction is an expected outcome of induction of labor. Combination methods of induction of labor may reduce the high failed induction rates reported by misoprostol or Foley catheter balloon alone.

In this study we propose a randomized trial whose aim is to find out if combined methods have a higher success rate.one arm will utilize misoprostol alone and the other combined misoprostol with Foley’s catheter. The outcomes will include successful induction, maternal and early neonatal outcomes. Failed induction or prolonged duration of induction to delivery may increase costs, patient anxiety, and if not monitored well especially in the setting of heavy workload may lead to poor neonatal outcomes.

If induction of labor using combined Foley and misoprostol can reverse or reduce these outcomes then it can change guidelines on induction of labor or for those patients at risk of failed induction.

A similar study has also not been carried out at our study setting.

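### Perinatal death after randomisation is not an outcome, so NICU admission, read alone, can lean towards the arm with more deaths before admission

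*Protocol*

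**What the plan says.** The third item under Specific Objectives in the protocol is "Determine and compare immediate maternal and perinatal outcomes". The components appear in one place only, under Secondary outcome: "Perinatal outcomes (APGAR, NICU admission". The Abstract gives a general label, "The outcomes will include successful induction, maternal and early neonatal outcomes", and the data analysis paragraph repeats the perinatal label; neither adds a component.

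Fetal demise appears as an indication for induction (Study setting) and among the inclusion criteria: "Intrauterine gestation, cephalic presentation, intact membranes, IUFD and Bishop score less than 6". Both refer to death before entry. Death after randomisation is not an outcome anywhere in the protocol.

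For analysis, the protocol specifies "intent to treat analysis using SPSS version 21" and "Proportions will be compares using Chi2 test, 95% CI, two tailed hypothesis with p significant at <0.05". It gives no separate denominator for fetuses alive at randomisation and no rule for a baby that dies before it could be admitted.

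On risk, the Introduction says of induction that "the procedure carries the risk of uterine hyper stimulation and rupture and fetal distress". The population is "Pregnant women admitted for induction of labor at KNH at gestational age of 28 weeks and beyond", so preterm fetuses are included.

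**The concern.** NICU admission is an outcome that death can prevent. A baby that dies in labour or in the delivery room may have been among the sickest, yet it adds nothing to the NICU numerator. If the two methods of induction differ in how often this happens, the arm with more such deaths has fewer babies left to be admitted, and its NICU rate falls for the wrong reason.

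Fetuses already dead at entry raise a different issue, because those deaths cannot be caused by the allocated method. The deaths at issue here happen after randomisation and could be. The protocol hopes its result may change induction guidelines, and it names rupture and fetal distress as hazards of induction. Its perinatal comparison should therefore not omit the gravest perinatal event, or rely on a measure that can move the wrong way when that event occurs.

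**Working it through.** **The plan's own figure.** The only computed figure is the sample size for the primary outcome. With success proportions of 0.74 and 0.90, their mean 0.82, and the stated multipliers 1.96 and 0.84:

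n = [1.96 × √(2 × 0.82 × 0.18) + 0.84 × √(0.74 × 0.26 + 0.90 × 0.10)]² / 0.16² = 89.2, rounded up to 90 per group.

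This matches the protocol. It matters here only because it supplies the denominator of 90. No figure is stated for any perinatal outcome.

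**Assumptions, none of them from the protocol.** Each arm has 90 fetuses alive at randomisation; 10%, 15% or 20% would need NICU in both arms; arm A has no deaths before admission and arm B has 2. Because women with fetal demise are eligible, the true number of live fetuses per arm would be below 90, and each death would then weigh slightly more.

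**Case 1: both deaths are among babies who would have been admitted.** Counts are rounded to whole babies (0.15 × 90 = 13.5, taken as 14).

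| Assumed need | Arm A | Arm B | Shift (points) | Arm B, survivors only |
|---|---|---|---|---|
| 10% | 9/90 = 10.0% | 7/90 = 7.8% | 2.2 | 7/88 = 8.0% |
| 15% | 14/90 = 15.6% | 12/90 = 13.3% | 2.2 | 12/88 = 13.6% |
| 20% | 18/90 = 20.0% | 16/90 = 17.8% | 2.2 | 16/88 = 18.2% |

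Arm B looks better by 2/90 = 2.2 points. Restricting to survivors removes little of this. At 15% need, death or NICU admission is 14 against 14: the composite removes the false advantage, but only the death component, 0 against 2, shows the harm.

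**Case 2: deaths are unrelated to NICU need.** Expected admissions in arm B are need × 88/90, so the shift is need × 2/90.

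| Assumed need | Arm A | Arm B | Shift (points) | Death or NICU admission, A vs B |
|---|---|---|---|---|
| 10% | 10.0% | 9.8% | 0.2 | 10.0% vs 12.0% |
| 15% | 15.0% | 14.7% | 0.3 | 15.0% vs 16.9% |
| 20% | 20.0% | 19.6% | 0.4 | 20.0% vs 21.8% |

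The composite in arm B is (need × 88 + 2)/90. Among survivors there is no shift in this case. NICU admission alone then shows almost nothing, while the composite moves in the right direction.

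**Against the precision of the trial.** At 15% and 90 per arm, the 95% confidence interval for a difference has half-width 1.96 × √(2 × 0.15 × 0.85/90) = 0.104, about 10 points. Even 3 deaths, all among babies needing NICU, give 11/90 against 14/90: z = 0.0333/√(0.1389 × 0.8611 × 2/90) = 0.65, two-sided p about 0.52.

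**Apgar.** A stillborn baby scored 0 counts against its arm. One left unscored is missing, which favours neither arm by rule. The protocol does not say which applies.

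**The case against.** The strongest reply is that the protocol never says a dead baby is counted as not admitted. That is correct. It is an inference from an intent-to-treat comparison of proportions with no separate denominator. Denominators and the handling of deaths are commonly left to a statistical analysis plan, which may exist. This disposes of any claim that the protocol contains a faulty counting rule. It does not dispose of the outcome list: the choice of outcomes belongs to the protocol, and a survivors-only denominator would not cure Case 1.

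A reader might also infer that the perinatal objective as a whole favours the arm with more deaths. The document does not support that, because Apgar is the other listed measure and can count such a death against its arm.

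A reader might further infer that the trial could declare a perinatal benefit on this account. The figures do not support that either: shifts of 0.2 to 2.2 points lie well inside an interval of about ±10 points.

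The exclusions under Study population (non-reassuring fetal status, growth restriction, anomalies, placenta previa, previous caesarean, other uterine surgery, high parity) remove several sources of intrapartum death and rupture, and the Introduction's remark on risk is a general principle, not an estimate for this trial. This stands, and it is a reason to expect few deaths.

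The bracket in the quoted list is not closed, so something may have been lost there. No other section supplies a death outcome. The limitation that there is no long-term follow-up does not explain the gap, since these deaths occur at or soon after birth.

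**Conclusion.** The point holds in a limited form. The protocol sets out to compare perinatal outcomes, names only Apgar and NICU admission, and makes death after randomisation an outcome nowhere. The NICU comparison, read alone, can lean towards the arm with more deaths before admission. That direction is conditional on how such babies are counted and on whether they would have needed NICU, and it does not extend to Apgar if stillbirths are scored 0.

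The size is uncertain and probably small: about 0.2 to 2.2 points for 2 deaths in one arm only, with 90 live fetuses per arm and 10 to 20% needing NICU, all assumed. This is too little to produce a significant NICU result by itself. The main loss is that a difference in deaths might not be reported as an outcome at all. Failed induction, the primary outcome, and the sample size are unaffected.

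**What to change.** Define the perinatal outcomes among fetuses alive at randomisation, so that women enrolled with fetal demise are outside these denominators. Then:

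- list perinatal death as an outcome, meaning intrapartum stillbirth or early neonatal death within the immediate follow-up;
- analyse NICU admission as death or NICU admission, with both components shown by arm;
- score Apgar 0 for intrapartum stillbirths.

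The cost is revised outcome wording and one or two data fields, taken from medical records that the protocol already plans to review. The small downside is a composite that joins events of unequal gravity and must be read with its components. Death itself will be descriptive: a split of 0 against 2 in 90 per arm gives a two-sided exact p of 2 × (90 × 89)/(180 × 179) = 0.50. The aim is that deaths are visible by arm, not that they are tested with power.
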